## Methods

### Study Design

The Fruitful Study is a 2-year mixed-method (qualitative and quantitative) study conducted in one hospital in each of the three participant countries (Bolivia, Guatemala, and Paraguay).

For the quantitative approach, a pre-post design will be used to (1) assess participants’ attitudes, knowledge, and behaviors before and after the training using a questionnaire (Tool 1); and (2) measure the level of implementation of tobacco control policies within the participant hospitals before and after the training using the Self-Audit Questionnaire (SAQ) (Tool 2). For the qualitative approach, focus groups and in-depth interviews of key persons will be used. With this methodology we aim to (1) explore the experience of adapting the training program in each of the participant hospitals; (2) ascertain participants’ experience undertaking the training program; and (3) understand the opportunities and barriers of undertaking online smoking cessation training programs in the participant countries. With the results of the focus groups, the research team aims to identify any difficulties in accessing and completing the course and to make the necessary improvements.

### Participants

The two main participant units from each organization are students and the hospitals themselves. The participant hospitals were selected because they had previously collaborated with the Training Unit of the ICO in training their health professionals in either electronic learning (e-learning) or in-person courses. The selected hospitals and their characteristics are shown in Table 1.

**Table 1 table1:** Characteristics of the selected hospitals.

Hospital	Country	Type of hospital	Workers, n	Beds, n
Instituto Oncológico del Oriente Boliviano de Santa Cruz de la Sierra	Bolivia	Public, urban oncology hospital	359	79
Instituto de Cancerología y Hospital [name] del Valle	Guatemala	University, public, urban oncology hospital	300	108
Instituto Nacional de Enfermedades Respiratorias y del Ambiente (INERAM)	Paraguay	University, public, respiratory hospital	746	151

Student participants were all health professionals and paraprofessional staff from the three participant hospitals. All health providers in the selected hospitals, including nurses, doctors, and other health professionals were invited to enroll in the training. Each local coordinator recruited participants from a variety of units and departments over a 6-month period through informative sessions, leaflets, and posters (designed to inform about the training program).

### Procedure and Timeline

#### Selecting a Suitable and Effective Training Program

The selected original training program was chosen because it was shaped using evidence-based guides, was originally designed for Spanish hospitals (culturally and organizationally similar to LAC hospitals), and is addressed to hospital workers. Furthermore, offering the course through an online platform has clear potential to reduce cost and increase training coverage within participant hospitals in less time.

The original course was developed in the online platform e-oncologia based on the in-person courses offered during the last 10 years by the Tobacco Control Unit of the ICO. The theoretical framework underpinning the training program is the Stages of Change Model [30], and the curriculum was developed with the content of numerous meta-analysis and clinical practice guidelines [16,31-34] (Figure 1). We created a fully referenced, online curriculum, with feedback from an expert advisory group that oriented the instructional design to ensure the course content was palatable for an online format and aligned with the learning objectives. The goals and program components (strategies, activities, services, etc) are depicted in Figure 2. The final curriculum content of the “Brief Intervention for Smoking Cessation Training Program” is composed of 4 modules (Textbox 1).

The 4 modules of the Brief Intervention for Smoking Cessation Training ProgramModulesModule 1 describes the tobacco epidemic, tobacco-related morbidity and mortality, second hand smoke, and measures included in the MPOWER strategy to tackle smoking.Module 2 provides orientation on how to assess the smoker, how to assess tobacco dependence and willingness to quit, and evaluate smoker self-efficacy, previous quit attempts, previous relapses, and so on.Module 3 introduces the efficacy of the different levels of attention and treatment orientations (eg, cognitive behavioral, psychodynamic, medication management) and presents the clinical settings where the intervention is possible (eg, inpatient, outpatient, ambulatory treatments). It explains in detail the 5As intervention model.Module 4 explains in detail the different tobacco cessation treatments available (nicotine replacement, bupropion, varenicline, and other treatments). It also provides orientation about the follow-up, strategies to improve the adherence of the treatment, how to identify withdrawal symptoms, how to deal with relapses, and so on.

This online training program includes (1) slides; (2) review exercises; (3) cases of 4 patients differing in demographics, diagnostic, stages of change, setting; and (4) problem solving exercises. The training provides several materials including slides, online tutorials with an expert tutor, recommended readings, patient cessation brochures, a therapeutic pocket guideline, and an organizational recommendation model to facilitate the implementation of tobacco cessation services in the hospital setting.

The original online course was firstly tested by 10 voluntary participants in Catalonia (Spain). Evaluation of the tobacco cessation program was thereafter tested in the ICO by 150 health professionals. This pilot test proved the acceptability of the training model, the adequacy of its contents, and obtained a high level of satisfaction in the trainees. This training initiative has also been shown to increase the level of implementation of tobacco control in Catalan hospitals (according to the SAQ) [35] and the engagement of health professionals [36,37], thus making them part of the solution. This course has been accredited by the Council of Oncology in Europe (ACOE) in support of Continuing Medical Education for physicians. Since its launch in November 2012 to June 2014 more than 1000 Catalan health professionals have taken this course.

Based on literature regarding attrition among online learners [38], and our own experience delivering online training to Catalan health workers, we anticipate that roughly 50% of participants will complete all components of the proposed activities.

**Figure 1 figure1:**
[figure not shown]
Conceptual framework.

**Figure 2 figure2:**
[figure not shown]
Program model.

#### Adaptation of the Material

The adaptation has been done with local partners and other stakeholders. First, a group of professionals with extensive experience in tobacco control in their country were selected for identifying and categorizing mismatches between the original materials and the new context. Experts expressed that the goal and objectives were aligned with the original program model (Figure 2). Since they approved the interface and the images employed as culturally acceptable, the same layout was used. However, we detected some mismatches (Textbox 2) that were modified in a version that was pilot tested by 8 to 10 volunteers in each country.

Identified mismatches that were later modified and pilot testedMismatchesLanguage background and literacy level in some of the terms used:The course was in Spanish from Spain, and the Spanish spoken in Bolivia, Guatemala, and Paraguay differs somewhat with respect to vocabulary, some expressions, and in some cases even in grammar structures.Description of the epidemiology smoking in Model 1:The original version included the situation in Spain, whereas the adapted version included the most updated data in Bolivia, Guatemala, and Paraguay.Tobacco cessation pharmacological treatment in Module 4 (nicotine replacement therapy, bupropion, varenicline) and settings where tobacco prevention and cessation services are performed in Spain (primary care, hospitals, quitlines, etc) were adapted to the current resources in each country.In case studies, the clinical simulations demonstrate the cultural characteristics of each country.Questions and answers of the assessment and evaluation were also changed according to the adapted contents.

Several aids were necessary in order to enroll students. Thus, local investigators suggested a double registration method through the online platform consisting of an independent method (first one) by which students generated their own credentials and a second one assisted by a computer technician who created the login credentials and helped them in the usage of platform. The second method was necessary since many students had little or no experience in pursuing online education.

#### Implementation Plan

This study is expected to last 24 months (from November 2014 to November 2016). Information on the various activities is depicted in the event planning timeline (Figure 3).

This paper was written during the 18th month of the study when the post-evaluation data was being gathered. During the training (months 6 to 13), each participant had 1 month to fill in the baseline evaluation, complete the online training, and take the exam. Participants were monitored by local coordinators that acted as champions and encouraged participants to enroll and complete the course. Coordinators set monthly meetings with personnel from the different units and services to increase the number of participants and support those enrolled to complete the course. In addition, during the implementation, coordinators from each hospital offered assistance to students with little or no computer skills. Technical support was mainly used by less educated health professionals (assistants and support health professionals) and older workers who were less familiar with the use of computers. They offered their assistance in logging into the online platform, filling out the questionnaires, completing the evaluation, as well as other technical support-related issues. Participants’ progress was monitored in real-time on the Web platform. The project coordinator at the ICO sent biweekly reports of the participants' progress to coordinators, and if necessary personal emails and videos that motivated the students to finish the course and complete the evaluations. Participants accessed the course using their electronic devices (mobile phones, tablets or computers) or the ones provided by their hospitals during and after working shifts. The hospitals from Guatemala and Paraguay made a library available with computers to facilitate students’ enrolment before or after their working hours. The hospital from Bolivia provided a computer room in which students had access to the course and the support of a technician during specific hours of the day. Therefore, the participating hospitals facilitated computer and Internet access at the workplace.

**Figure 3 figure3:**
[figure not shown]
Event planning timeline.

##### Formative Evaluation

The formative evaluation will assess the adoption, implementation, and maintenance of the training program. We will measure program coverage, completion rates, fidelity with the training program, usage of the materials, and the satisfaction with the training. We will use qualitative (focus groups and interviews) and quantitative methods to gather this information. The indicators linked to the performance of the program are (2) number of participants; (2) characteristics of the participants (profession, units, sex, age); (3) number of hours dedicated to the training program; (4) program performance and fidelity to the curriculum plan (whether the students completed all the modules, the exercises as planned); (5) service utilization or dosage use of the training (time applied for undertaking the course, number of downloads of the materials, etc); and (6) opinions, experience, perceptions, and satisfaction with the training course.

##### Summative Evaluation

We will investigate the short and intermediate outcomes by measuring the impact of the smoking cessation training program within the participant hospitals using quantitative methods (pre-post design). This will include the level of implementation of tobacco control policies within the participant hospitals before and after the training by using the SAQ (Q1) and participants’ attitudes, knowledge, and behaviors before and after the training using a questionnaire (Q2).

### Instruments

#### Tool 1

To assess differences in tobacco control polices implemented within the hospitals we will use the European Network of Smoke free Hospitals (ENSH) SAQ [35]. This tool was developed for the ENSH-Global Network for Tobacco Healthcare Services. The questionnaire is composed of the following 10 policy standards: (1) commitment (6 items); (2) communication (4 items); (3) education and training (4 items); (4) identification and cessation support (8 items); (5) tobacco control (5 items); (6) environment (6 items); (7) healthy workplace (5 items); (8) health promotion (1 item); (9) compliance monitoring (2 item); and (10) and policy implementation (1 item). Each item is scored 1 (not implemented), 2 (less than half of the aspects are implemented), 3 (more than half are implemented), or 4 (fully implemented). The maximum score of the ENSH SAQ is 168 points, calculated as the sum of the 10 standards [35]. At baseline, the SAQ provides information on the tobacco control policies undertaken within the organization. Once it is used to monitor the project, the instrument detects the fulfilled standards and the areas for improvement.

#### Tool 2

Trainers’ attitudes, knowledge, and behaviors will be assessed using a questionnaire composed of 63-items. The website-delivered questionnaire is emailed to the participants at baseline and 3 months after finishing the training. The questionnaire, designed by Sheffer et al [40], takes 30 to 40 minutes to complete. The questionnaire gathers information about the provider's sex, tobacco use history, previous tobacco cessation education, level of pro-activity addressing tobacco use, and perceived success in helping patients stop using tobacco [40]. Perceived knowledge and attitudes about treatment of tobacco use will be determined by assessing the levels of (1) motivation; (2) knowledge about tobacco cessation; (3) self-efficacy; (4) importance of providing tobacco use interventions; (5) effectiveness of interventions; (6) importance of barriers; (7) readiness; and (8) level of tobacco cessation intervention provided assessed by the 5A’s model, an evidence-based framework that helps health professionals to structure smoking cessation interventions by identifying all smokers and offering support to help them quit. The 5A's model consists of 5 components: ask, advice, assess, assist, and arrange follow-up. All items are assessed on a discrete scale from 0 (none or not at all) to 10 (the most possible). The pre-test will be administered immediately prior to the training. The post-training assessment is composed of a 37-item questionnaire assessing providers’ knowledge, attitudes, and behaviors, as assessed in the pre-test.

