### Hypothesis

Our primary hypothesis is the participants in the online tobacco cessation training program will increase their tobacco-related knowledge, attitudes, and behaviors by the 6-month follow-up, as compared to baseline conditions prior to the training. Our secondary hypothesis is that participating hospitals will exhibit greater tobacco control progression, commitment, and implementation of tobacco cessation services.

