## Results

We have enrolled 281 hospital workers (105 from Bolivia, 88 from Guatemala, and 88 from Paraguay). The overall average completion rate is 66.2% (186/281). At the time of submission of this paper, data collection for the post-evaluation was underway. Evaluations will finish in November 2016 and results are expected by the beginning of 2017. Results of this study will be reported in two follow-up papers: one about the formative evaluation and the other about the summative evaluation.

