### Limitations and Strengths

Health professionals and paraprofessional staff from the three countries will be invited to voluntarily participate in the project. We will be able to determine whether the recruitment process used by each coordinator affects both the number of participants recruited and the commitment to start and finish on time. We hypothesize that as they agree to join, they will be highly motivated to pursue the course and we expect many of them to succeed on their own. However, participants may have varying levels of computer skills and Internet usage that could affect their course enrollment and progression. Online training programs also require devices for their use (ie, computers, tablets or mobile phones with app capabilities) and a high speed Internet connection. Although Internet services and technological devices are rapidly growing in low-income countries [42] it may not be the same as in HICs. Nevertheless, the course could be followed by these platforms facilitating the connectivity among users (tablets, mobile phones) being able to complete the training program at home or in their working hospitals. We foresee that many of the students will be using mobile phones as their primary access to the course, because mobile phones are more accessible in these countries than computers [42]. Furthermore, the participants could have different knowledge in smoking cessation interventions within participant hospitals and among the different countries. This could make comparisons among participant countries very interesting. The fact that we included baseline and post-intervention evaluations will permit the evaluation of these differences.

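### The post-training questionnaire is timed from finishing the course, so participants who do not finish have no defined post assessment, although the primary hypothesis covers all participants

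*Protocol article*

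**What the plan says.** Under Instruments, Tool 2, the article sets the timing of the trainee questionnaire: "The website-delivered questionnaire is emailed to the participants at baseline and 3 months after finishing the training". It gives no other time point for people who do not finish.

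The Hypothesis section is about participants, not completers, and names a different time: "the participants in the online tobacco cessation training program will increase their tobacco-related knowledge, attitudes, and behaviors by the 6-month follow-up". Sample Size also works from baseline to 6 months.

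The article treats non-completion as common. Before the study (Selecting a Suitable and Effective Training Program): "we anticipate that roughly 50% of participants will complete all components of the proposed activities". In Results: "The overall average completion rate is 66.2% (186/281", from this enrolment: "We have enrolled 281 hospital workers (105 from Bolivia, 88 from Guatemala, and 88 from Paraguay".

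On course timing, the Implementation Plan says that "each participant had 1 month to fill in the baseline evaluation, complete the online training, and take the exam". The same section places training in months 6 to 13, says the article was written in month 18, and has the study ending in November 2016 (month 24). Results also has evaluations running to November 2016.

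**The concern.** A pre-post comparison can use only people who have a post measurement. If that measurement is requested a set time after an event that a third to a half of participants never reach, those people drop out of the comparison by design. No later analysis plan can recover answers that were never requested.

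The loss is unlikely to be random. Non-finishers received less of the course. Limitations and Strengths acknowledges that "participants may have varying levels of computer skills and Internet usage that could affect their course enrollment and progression". Adaptation of the Material adds that many students were new to online education. A gain measured in finishers would then describe the more motivated and computer-literate staff, yet it could be read as the result of offering the course to the whole workforce of these hospitals, which is what the primary hypothesis addresses.

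**Working it through.** **Inputs from the article.** Enrolled: 105 + 88 + 88 = 281. Completed: 186. Expected completion: about 50%. Anticipated gain: 40% (Sample Size) and 30% to 40% (Principal Findings). Minimum sample: 43 per hospital, including 15% dropout.

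**The article's own figure.** 186/281 = 0.662, which agrees with the stated 66.2%. Non-finishers: 281 − 186 = 95, and 95/281 = 33.8%.

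**Gain over all enrolled.** Let c be the proportion completing, G the gain in finishers, and r the non-finisher gain as a fraction of G. Then

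gain over all enrolled = c × G + (1 − c) × r × G.

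The article gives no value for r, so it is an assumption and a range is shown. The formula also assumes that gains average across the two groups, which is exact if gain is on an absolute scale or if the groups share the same baseline mean.

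| Completion c | Finisher gain G | r = 0 | r = 0.5 | r = 1 |
|---|---|---|---|---|
| 66.2% (observed) | 40% | 26.5% | 33.2% | 40% |
| 66.2% (observed) | 30% | 19.9% | 24.9% | 30% |
| 50% (expected) | 40% | 20% | 30% | 40% |
| 50% (expected) | 30% | 15% | 22.5% | 30% |

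Example: 0.662 × 40 + 0.338 × 0.5 × 40 = 26.5 + 6.8, which is 33.2 before rounding the terms.

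For a 40% finisher gain, the possible overstatement is 0 to 40 − 26.5 = 13.5 points at 66.2% completion, and 0 to 20 points at 50%.

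**Against the anticipated 30% to 40%.** With G = 40% and c = 66.2%, the all-enrolled gain stays at or above 30% if r is at least (30 − 26.5)/(0.338 × 40) = 3.5/13.5, about 0.26. With G = 30%, any r below 1 takes it under 30%.

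**Power.** Allowing 15% dropout, 43 per hospital leaves 43 × 0.85, about 36 evaluable. At the overall completion rate, actual enrolment gives 0.662 × 88, about 58, to 0.662 × 105, about 69 finishers per hospital. At 50% it gives 44 to 52. All exceed 36, so the issue is bias and not power.

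**Timing.** With a course window of up to 1 month, 3 months after finishing is at most about 1 + 3 = 4 months after baseline. That is not the 6 months in Hypothesis and Sample Size. Training ended by month 13, so 4 months after baseline fell by about month 17, before the article was written in month 18. Evaluation then had 24 − 18 = 6 months left.

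**The case against.** The strongest reply is that the article nowhere restricts the questionnaire to finishers. It is sent to the participants at both times, and since everyone had a 1-month window, finishing could mean the end of that window, which everyone reaches. This stands as far as it goes: that only finishers are measured is an inference from the stated anchor. But the article's own usage favours completion. The Implementation Plan describes messages urging students to finish the course, and Limitations and Strengths speaks of finishing on time as something participants may or may not do. If the window was meant, the sentence still needs correcting.

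A reader might also infer that the documents show an upward bias. They do not. The non-finisher gain is unknown, and the bias is zero if it equals that of finishers. The text says only that computer skills could affect progression, and it mentions technical support for older and less educated staff as a help, not as evidence that they failed to finish. No comparison of finishers with non-finishers is given.

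The figure of 95 is also an upper count of recoverable people. Results does not define completion, and some of the 95 may lack baseline data or may have missed only the exam.

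Finally, Evaluation Design treats participation as its own outcome level, so completion will be reported beside the gain. That helps a careful reader, but it does not answer a hypothesis about participants in general.

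The article names no analysis set. A condensed article may leave that to the full protocol or analysis plan, and it is not part of this point.

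**Conclusion.** The point holds in this form: the post assessment is anchored to finishing, so 95 of 281 enrolled (33.8%), or about half on the article's own forecast, have no defined post assessment, although the primary hypothesis is about all participants. Followed literally, the comparison covers finishers and probably overstates the gain for participants as a whole. With an assumed 40% gain in finishers and observed completion, the overstatement lies between 0 and 13.5 points. The upper end requires non-finishers to gain nothing; the lower end requires them to gain as much as finishers. The direction is likely because non-finishers had less exposure, but it is not demonstrated. The documents do not support saying that the article restricts measurement to finishers or that the gain is known to be biased upward. Because the gap lies in a stated collection rule and cannot be repaired after evaluation closes, it should be corrected while evaluation is open.

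**What to change.** 1. Restate the schedule so that the post questionnaire falls a fixed time after enrolment, or after the end of the 1-month window, for every participant. Reconcile that time with the 6-month follow-up in Hypothesis and Sample Size.
2. While evaluation remains open (to November 2016), send the questionnaire to every non-finisher with baseline data and record the elapsed time since baseline. A 4-month date had already passed for almost all of them when the article was written, so these answers will be late and should be labelled as such.
3. Report the pre-post change for all participants with baseline data. Include a bound that sets the change to zero for those without post data; this is conservative provided that they did not get worse.
4. Report finishers separately, with a baseline comparison of finishers and non-finishers.
5. If non-finishers cannot be surveyed, limit the stated conclusion to course completers.

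The cost is up to 95 extra emails, a modest amount of analysis, some off-schedule responses and a probably smaller estimated gain.
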